#### Monitoring

##### Data monitoring and auditing

The ABRACE: Telehealth Study does not have a data monitoring committee either planned auditing trial conduct due to limited resources. We reason that this committee would not be mandatory due to the characteristics of interventions and outcomes, despite its high value for the overall quality of the trial. [name], [name], and [name] will have access to all data and interim analysis and make the final decision to terminate the trial.

##### Harms, ancillary, and post-trial care

The adverse events will be managed according to the National Institute of Aging (40). A serious adverse event is any unfavorable medical occurrence, with risk of death or disability of the participant, which requires hospitalization. The identification, possible solutions, and documentation of adverse events are based on discussion and analysis between the principal investigator, study directors, study managers, and medical team. For any injuries suffered during trial enrollment related to the study (after adjudication by these researchers), we plan contingency actions to provide participants primary health care and guidance. Every effort will be made to prevent any unwanted events.

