#### Criteria for discontinuing allocated interventions

Participants may be discontinued from the study for safety reasons or withdrawal of participant’s consent. For participants allocated to any group, medical advice, disease complication, or a severe health event during the study, which precludes attendance to intervention sessions, are considered criteria for interrupting participation in the study. Even participants who have discontinued the interventions will continue to be contacted by the study and invited for final evaluations.

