### Safety outcomes

A medical clearance for physical exercise provided by their oncologist is requested for each patient. We will collect and manage spontaneously reported adverse events. Such events will be classified according to their severity (i.e., mild, moderate, severe), predictability (i.e., expected or unexpected), and potential relation with study procedures (i.e., definitely related, possibly related, or unrelated) [37]. All cases of adverse events will be discussed and, if necessary, adjudicated by at least two out of the following investigators: principal investigator ([name]), study manager ([name]), and medical and expert consultants.

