Telehealth interventions may optimize cancer care due to the potential to enhance adherence rates, remove barriers, support access and motivation, reduce costs, be time-efficient, and combine both clinician and participant feedback [5, 34]. Ongoing trials have contributed to exploring the positive effects of online exercise programs in the oncology population. Currently, a randomized controlled trial employing jumping training delivered by recorded videos and including behavioral and diet counseling has been implemented to improve bone health and clinical outcomes in pediatric cancer survivors [17]. Furthermore, an innovative single-arm study assesses the feasibility and acceptability of a group-based exercise intervention using teleconferencing in older patients who have received or are undergoing liver cancer treatment [40]. However, web-based interventions targeting behavior change through real-time monitoring and assisting exercise techniques, progressions, and compliance to mitigate cancer-related fatigue and promote a better quality of life and mental health still need more investigations. To our knowledge, this is the first randomized clinical trial using face-to-face videoconference to supervise exercise evaluating clinically relevant outcomes directly related to cancer treatment in oncology participants.

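### The serious adverse event definition joins hospitalisation to risk of death or disability, so events meeting only one of these conditions would not be labelled or counted as serious

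*Protocol article*

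**What the plan says.** The section Harms, ancillary, and post-trial care of the protocol article defines seriousness in one sentence: "A serious adverse event is any unfavorable medical occurrence, with risk of death or disability of the participant, which requires hospitalization". The sentence before it points to an outside source: "The adverse events will be managed according to the National Institute of Aging (40", where 40 is a reference number.

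The Safety outcomes section sets out how events are gathered and classified. On gathering: "We will collect and manage spontaneously reported adverse events". On classification: "Such events will be classified according to their severity (i.e., mild, moderate, severe), predictability (i.e., expected or unexpected), and potential relation with study procedures". All events are to be discussed and, where needed, adjudicated by at least two members of a named group of investigators and consultants.

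The section on discontinuing allocated interventions has its own triggers: "medical advice, disease complication, or a severe health event during the study". On oversight, the Data monitoring and auditing section states: "The ABRACE: Telehealth Study does not have a data monitoring committee".

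**The concern.** The only alternative inside the definition is between death and disability. Hospitalisation is added as a further requirement, so the sentence sets joint conditions where a reader would expect a list of separate criteria. Followed literally, it could leave a fatal event that happened outside hospital without the serious label.

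The setting makes such cases foreseeable. Participants are women with stage I–III breast cancer on chemotherapy, or on radiotherapy or immunotherapy after it. They take part from home by video call. With no data monitoring committee, classification rests with the study's own investigators and consultants, and the wording they apply decides what the safety report counts as serious. At stake is the accuracy of that count.

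**Working it through.** No figure in the document is to be reproduced, because the point concerns the logic of a definition. The check has three steps.

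**1. Parse the sentence.** Let D stand for risk of death or disability, and H for an event that requires hospitalisation. A fatal event satisfies D. As written, serious = D AND H. If the elements were alternatives, serious = D OR H.

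| Event | D | H | As written | As alternatives |
|---|---|---|---|---|
| Life-threatening or disabling, admitted | yes | yes | serious | serious |
| Death, life-threatening or disabling event, not admitted | yes | no | not serious | serious |
| Admission without risk of death or disability | no | yes | not serious | serious |
| Neither | no | no | not serious | not serious |

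The wording labels one of the four combinations serious, and the alternative reading labels three. They differ in the second and third rows. Treating the last clause as a non-restrictive remark does not remove the problem. The sentence would then assert that every serious event requires hospitalisation, and the second row would still be excluded.

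**2. Look for a passage that widens the definition.**

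- *Safety outcomes* classifies by severity, predictability and relation to study procedures. Severity is not seriousness, and the section contains no seriousness criterion.
- *Criteria for discontinuing allocated interventions* speaks of a severe health event, but neither defines it nor ties it to the serious category.
- *Harms, ancillary, and post-trial care* cites the National Institute of Aging source for how events are managed, not for what counts as serious. Its content is not shown. Its number, 40, also appears in the Discussion for a single-arm teleconference exercise study in "older patients who have received or are undergoing liver cancer treatment [40", so the pointer does not clearly lead to an adverse event guideline.

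None of these changes the result of step 1.

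**3. Trace the consequence.** An event in the second or third row, if reported, still enters the adverse event record and is discussed under Safety outcomes. What it loses is the serious label. The document makes no stopping rule, reporting deadline or planned analysis depend on that label.

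The Sample size section gives about 30 women, about 15 per arm. As an illustration only, assume one woman in an arm has a single event, and it falls in the second or third row. Her arm's proportion with a serious event then changes by 1/15 = 6.7 percentage points, and the whole-trial proportion by 1/30 = 3.3 percentage points. How often such events occur cannot be derived from the document.

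**The case against.** The strongest reply is that this is loose English and not an operating rule. The article has other slips of language. It refers to a full protocol that is not shown, and it cites outside sources for adverse event handling and classification. The investigators may have meant alternatives and may be applying them. That is possible and limits any claim about how events are actually being counted. It does not settle the matter: the article chose to state a definition, so this is not a detail left to a fuller document, and a source that is not shown cannot correct an explicit sentence.

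A second reply is that little depends on the label. Reported events are collected without a seriousness threshold, all are discussed, discontinuation has its own triggers, and withdrawals are documented case by case. This stands, and it confines the point to classification and counting.

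It also rules out stronger readings that a reader might infer:

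- That deaths outside hospital would go unrecorded. The Safety outcomes section does not restrict collection to serious events.
- That, without a data monitoring committee, seriousness is the trial's chief safety gate, so its safety conclusion would be falsely reassuring. The document gives the label no such role and states no safety hypothesis or comparison of serious-event rates.
- That the three-level severity scale is defective because it has no fatal grade. Nothing prevents a fatal event from being graded severe, and a separate grade is a matter of preference.

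**Conclusion.** The point holds for the sentence as written. Events that meet only one of the two conditions would not be labelled or counted as serious, and out-of-hospital deaths are among them. Event capture, the discontinuation criteria, the sample size and the fatigue analysis are unaffected.

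The conclusion assumes that the sentence is applied literally and that no document outside those shown overrides it. The document does not say whether any event already recorded is affected. This is a modest correction to a stated rule. It is worth making because, in a trial of this size, a single reclassified event is visible in the safety table.

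**What to change.** 1. Reword the definition so that its own elements are alternatives: an event is serious if it involves death or risk of death, OR disability, OR hospitalisation.
2. Reconcile the sentence with the adverse event source it cites, and correct the reference number if 40 is meant for the liver cancer exercise study.
3. Before safety is reported, classify all logged events by the corrected definition and state in the report which definition was used.

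The cost is one sentence, one citation check and a re-read of whatever events have been logged for about 30 women. The article appeared in January 2023, with recruitment planned to run to March 2023, so on the planned dates there was time to do this before final results. The downside is that the serious-event count may rise.

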##### Dissemination policy

We aim to disseminate the methods and findings of the ABRACE: Telehealth Study to as many stakeholders as possible. Therefore, our dissemination plan after trial completion includes inviting the participants to watch presentations about study design, findings, and interpretation, and the results of this study, whether positive, negative, or inconclusive, will be submitted to a peer-reviewed international journal for possible publication. All information regarding the full protocol, participant-level dataset, and statistical code will be available from the corresponding author on reasonable request.

## Discussion

This trial is strengthened in the attempt to propose an exercise protocol performed at home, via telehealth, and test its effectiveness in relevant outcomes for the quality of life of patients with breast cancer. The importance of exercise during and after treatment of these patients is becoming increasingly apparent, and it is essential that professionals in the field of physical exercise find strategies to reduce the barriers to practice and increase adherence. Home-based programs that incorporated technology to support interventions reported attendance rates greater than 70% [34]. In addition, this study is enhanced by using guided exercise with supervision. Home-based exercise does not necessarily mean “unsupervised” exercise [31]. Currently, videoconferencing platforms allow exercise professionals to demonstrate and provide exercise guidance virtually in individual or group sessions [5].

The feasibility and quality of telehealth exercise interventions have been underexplored, and their effectiveness remains unclear in the exercise oncology setting [5, 44]. Previous studies using technology to apply interventions with physical activity in the cancer population have reported improvements in outcomes such as physical activity levels, weight loss, and high adherence [20, 34, 44]. Notwithstanding, the effectiveness in outcomes related to fatigue, quality of life, anxiety, and depressive symptoms remain unidentified [34, 44]. The only study that investigated exercise intervention via telehealth using a face-to-face videoconference platform to supervise cancer survivors directly reported 94% adherence in those who choose to participate in the training group [13]. However, the authors did not find improvements in sedentary time or physical activity in the participants (during COVID-19 lockdown), nor evaluated outcomes directly related to side effects of treatment.

Telehealth interventions may optimize cancer care due to the potential to enhance adherence rates, remove barriers, support access and motivation, reduce costs, be time-efficient, and combine both clinician and participant feedback [5, 34]. Ongoing trials have contributed to exploring the positive effects of online exercise programs in the oncology population. Currently, a randomized controlled trial employing jumping training delivered by recorded videos and including behavioral and diet counseling has been implemented to improve bone health and clinical outcomes in pediatric cancer survivors [17]. Furthermore, an innovative single-arm study assesses the feasibility and acceptability of a group-based exercise intervention using teleconferencing in older patients who have received or are undergoing liver cancer treatment [40]. However, web-based interventions targeting behavior change through real-time monitoring and assisting exercise techniques, progressions, and compliance to mitigate cancer-related fatigue and promote a better quality of life and mental health still need more investigations. To our knowledge, this is the first randomized clinical trial using face-to-face videoconference to supervise exercise evaluating clinically relevant outcomes directly related to cancer treatment in oncology participants.

## Trial status

The recruitment period for the ABRACE: Telehealth study is planned to range from March 2021 to March 2023. This is the first version of the manuscript and is accompanied by a description of existing amendments (Additional file 0^3^).

## Data Availability

Not applicable. This manuscript does not contain any data.

## Abbreviations

ABRACE Telehealth: Adaptations to Breast Cancer and Exercise Using Telehealth
MTHE: Multicomponent Training Group plus Health Education
HE: Health education group
RPE: Rating of perceived exertion
